---

## Study Status

Record Verification: May 2021

Overall Status: Completed

Study Start: January 31, 2021 [Actual]

Primary Completion: April 4, 2021 [Actual]

Study Completion: April 4, 2021 [Actual]

## Oversight

U.S. FDA-regulated Drug: No

U.S. FDA-regulated Device: No

U.S. FDA IND/IDE: No

Human Subjects Review: Board Status: Approved

Approval Number: 00039312

Board Name: University of Toronto Research Ethics Board

Board Affiliation: University of Toronto

[contact]

Email: [contact]

Address:

Data Monitoring: No  
FDA Regulated Intervention: No

## Study Description

**Brief Summary:** The COVID-19 pandemic and the accompanying lockdown measures have made mental health a pressing public health concern. Acts that focus on benefiting others—known as prosocial behaviors—offer one promising intervention that is both flexible and low cost. However, neither the range of emotional states prosocial acts impact nor the size of those effects is currently clear, both of which directly influence its attractiveness as a treatment option. Using a large online sample from Canada and the United States, the investigators will examine the effect of a three-week prosocial intervention on two indicators of emotional well-being (happiness and the belief that one's life is valuable) and mental health (anxiety and depression). Respondents will be randomly assigned to perform prosocial, self-focused, or neutral behaviors each week. Two weeks after the intervention, a final survey will assess whether the intervention has a lasting effect on mental health and emotional well-being. The results will illuminate whether prosocial interventions are a viable approach to addressing mental health needs during the current COVID-19 pandemic, as well for those who face emotional challenges during normal times.

**Detailed Description:** This study is intended to be published as a registered report. The details of the study design are likely to change somewhat during the review process. However, below is the current plan:

The investigators will examine the effects of prosocial behavior using a 3-week experimental intervention, followed by a follow-up assessment at 5 weeks. At baseline the research team will measure participants' emotional well-being and mental health. Emotional well-being will be assessed using happiness and feeling that one's life is valuable, which is a facet of sense of meaning in life. Mental health will be measured as depression and anxiety. At the end of the baseline survey the researchers will randomly assign participants to one of three experimental conditions (between-subjects design). In each condition, respondents will be asked to perform certain types of behaviors for the first three days of each week, as detailed later in this protocol.

Respondents will be contacted for the first three days each week and asked to report what they did. At the end of weeks 1, 2, and 3 they will complete a longer survey that repeats the same measures of emotional well-being and mental health used at baseline. At this point the intervention will be complete. The investigators will recontact respondent two weeks later (at the end of week 5) to assess whether the intervention has a lasting effect on mental health and emotional well-being. This final survey will also include a measure of whether or not respondents continued their assigned behaviors following the end of the intervention. This measure might be useful for explaining any lasting effects in exploratory analyses.

The expected effect size is  $d = 0.19$ . The research team will assess experimental effects using multiple linear regression. The models will include indicator variables for experimental conditions as well as controls for baseline levels of happiness, valued life, depression, and anxiety. These baseline measures should be unrelated to experimental conditions (which will be randomly assigned) so including them will increase the efficiency of estimates. Under the assumption that these variables will account for at least 50% of the variance in the outcomes, the sample size needed to detect an effect of size  $d = 0.19$  with 95% power is  $N = 357$  or approximately 360 per condition. The

expected attrition rate is 30% after baseline which means that the investigators will sample  $360/0.7 = 514$  per condition.

The research team will post the baseline survey in two batches. The first batch will contain half the sample ( $N = 771$ ), and will be used to gauge the attrition rate (see data exclusion criteria). The sample size of the second batch will be adjusted as needed to try and capture the desired number of respondents per experimental condition. This will lower the size of the second batch if attrition rates are lower than expected or increase the size of the second batch if attrition rates are higher than expected. If a sufficient sample size has not been obtained at this point, the investigators will repeat the process until at least 350 respondents in each experimental condition are recruited. To be clear, the stopping rule for recruiting sample participants does not require estimating any of the effects of interest in the study (i.e., it does not depend on the anticipated effect size). The only factor is whether a sufficient number of respondents have been recruited for each experimental condition.

Obtaining a sufficient per-condition sample size might take several days. The researchers plan to begin sampling on a Sunday and continue sampling (if needed) on Monday. This means respondents will finish their first three days of the study on either Wednesday or Thursday. In either case, the investigators will distribute the end of week 1 survey the following Sunday, which will then put both groups of respondents on the same schedule for the remainder of the study. The researchers will try to recruit the full sample during this initial recruitment phase, as this will simplify administering the study. However, if initial sampling does not yield a sufficient sample size, the researchers will repeat the sampling procedure each week until a sufficient number of respondents is obtained. In this case, the study will be administered to different “cohorts” of respondents spaced a week apart.

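### Batch 2 is sized by setting a baseline-stage loss rate against a 30% allowance defined as loss after baseline, so the adjustment, up or down, uses the wrong rate

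*Protocol*

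**What the plan says.** All of this is in the Protocol. The Detailed Description (under Study Description) derives the sample size from a standardised effect of 0.19, baseline covariates explaining half the outcome variance, and 95% power, giving 357, rounded to 360 per condition. It then adds an allowance for dropout: "expected attrition rate is 30% after baseline which means that the investigators will sample" 360/0.7 = 514 per condition.

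The recruitment paragraphs that follow split the sample in two: "The first batch will contain half the sample ( $N = 771$ ), and will be used to gauge the attrition rate (see data exclusion criteria"). The second batch is then adjusted against expectation. "This will lower the size of the second batch if attrition rates are lower than expected", and it is raised if they are higher. If numbers still fall short, the process repeats until at least 350 per condition have been recruited. The protocol says that only the number recruited governs stopping.

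On timing: "The researchers plan to begin sampling on a Sunday and continue sampling (if needed) on Monday". Both groups get the end-of-week-1 survey on the following Sunday, and the team aims to fill the whole sample in this initial phase. Weekly cohorts are the fallback.

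The Eligibility section lists six exclusion criteria. They cover speed, completeness, open-text quality, IP address and technical failure at the baseline survey, and declining to continue (at the end of baseline or by private correspondence). Respondents removed under criteria 1 to 5 are replaced as recruitment proceeds. For technical failure the same person is tried again first, then replaced.

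**The concern.** The allowance of 154 extra respondents per condition (514 − 360) is there to absorb loss between baseline and the later surveys at weeks 1, 2, 3 and 5. Batch 1 cannot show that loss in time to size batch 2. What it can show is how many people fail or decline at baseline, and the protocol's own pointer to the exclusion criteria suggests that this is what will be counted.

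If that count comes out below 30%, the rule reads it as good retention and cuts batch 2, although nearly all the follow-up period is still to come. If it comes out above 30%, the rule enlarges batch 2 for a reason unrelated to retention. The first case costs power, in a protocol that names adequate power as a central aim. The second costs money.

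**Working it through.** **1. Reproduce the plan's figure.** Inputs from the Detailed Description: "The expected effect size is $d = 0.19"; R² = 0.5 ("Under the assumption that these variables will account for at least 50% of the variance in the outcomes"); 95% power. The significance level is not stated, so two-sided 5% is assumed. The residual SD is √(1 − 0.5) = 0.707.

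n per condition = 2 × (1.960 + 1.645)² × 0.5 / 0.19² = 12.995 / 0.0361 = 360.

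This matches "with 95% power is $N = 357$ or approximately 360 per condition"; power at 357 is 94.8%. A one-sided 5% test would need 300, so two-sided 5% is the reading that fits. Inflation: 360/0.7 = 514.3. Total: 3 × 514 = 1542, and half is 771, the stated first batch. The plan's arithmetic is sound.

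**2. Set the two rates side by side.**

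| | Rate in the sample size calculation | Rate available from batch 1 |
|---|---|---|
| Event | Loss after baseline | Exclusion or refusal at baseline |
| When visible | From the end-of-week-1 survey onwards | Once baseline responses are in |
| Handling | Inflation from 360 to 514 | Replacement under Eligibility |

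Sunday entrants finish their first three daily reports on Wednesday and Monday entrants on Thursday. The first end-of-week survey reaches both groups on the following Sunday. Any batch posted in the initial phase is therefore sized before a single end-of-week return exists.

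**3. Consequence if the early rate is used.** Let *a* be the early loss rate. The document gives no value for it, so the values below are illustrative. Assume that excluded respondents are replaced and that later loss is the protocol's own 30%.

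- Entered per condition = 360/(1 − a)
- Batch 2 = 3 × entered − 771
- Retained per condition = 0.7 × entered
- Power = Φ(0.19/0.707 × √(retained/2) − 1.96)

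| Early loss | Entered per condition | Batch 2 | Retained per condition | Power |
|---|---|---|---|---|
| 30% | 514 | 772 | 360 | 95.0% |
| 20% | 450 | 579 | 315 | 92.1% |
| 10% | 400 | 429 | 280 | 88.9% |
| 0% | 360 | 309 | 252 | 85.5% |

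The 772 in the first row differs from 771 only because 514.3 was not rounded down. For a = 10%: 0.2687 × √140 − 1.96 = 1.22, and Φ(1.22) = 0.889.

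**4. Does the floor catch it?** The floor counts people recruited. With 350 recruited and 30% later loss, 0.7 × 350 = 245 are retained and power is 84.5%. Every row of the table has more than 350 entrants, so none would trigger a further cohort.

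**The case against.** The strongest reply is that the pointer to the exclusion criteria shows that attrition here simply means baseline exclusions, which can be observed at once. That is a fair reading of the recruitment paragraph, but it does not rescue the rule, because the expectation it is compared with is explicitly loss after baseline. If exclusions were instead meant to use up the allowance, without replacement, about 360 eligible respondents per condition would start follow-up whatever the early rate. Then 0.7 × 360 = 252 would remain, with 85.5% power. The gradient in the table thus depends on replacement, which is what the Eligibility section describes.

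Some stronger readings are tempting but not supported:

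- A reader might infer that batch 2 goes out within a day of batch 1. The text does not tie batch 2 to Monday, and it says that recruitment may take several days. The point needs only that batch 2 precedes the first end-of-week survey.
- A reader might infer that the rule can only shrink recruitment. It works in both directions, and shrinkage needs an early rate below 30%.
- A reader might infer that nothing after baseline is visible. A first daily report could be due from Sunday entrants on Monday. It is weak information on five-week retention, but it is not nothing.
- A reader might take the actual enrolment of 1328 (Study Design), below 1542, as proof that batch 2 was cut this way. The document does not say why enrolment was lower, or whether 1328 is before or after exclusions.

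It is also true that the design was described as likely to change in review, that the study is complete, and that power stays at about 85% or more in every row of the table. These limit the severity of the point without removing the mismatch. The floor of 350 shares a root with this point, since both count entrants and not those retained. A team that ignored the floor would still size batch 2 from the wrong rate.

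**Conclusion.** The concern holds in this form: the second batch is adjusted by comparing a baseline-stage loss rate, plus at most a few daily reports, with an allowance defined as loss after baseline. The rate that the allowance needs does not exist at that moment, and the exclusions that do exist are already handled by replacement.

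The harm is conditional. If early loss is below 30% and later loss is the planned 30%, fewer than 360 per condition are retained. For early loss between 20% and 0%, the chance of missing a true effect of 0.19 rises from 5% to between about 8% and 15%. This rests on an assumed two-sided 5% level (which reproduces the plan's 360), R² of 0.5, replacement of exclusions, and early rates chosen for illustration. The document does not show that this happened in the trial. The point merits correction but is not fatal to the design.

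**What to change.** Reword the recruitment rule in the Detailed Description so that:

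1. batch 1 is used only to estimate the baseline exclusion and refusal rate, and so how many baseline surveys must be posted per eligible entrant;
2. the 30% allowance for loss after baseline stays fixed when batch 2 is sized, so that 514 eligible respondents per condition enter;
3. observed end-of-week survey returns are used only to size the later weekly cohorts that the protocol already permits;
4. attrition and exclusion are kept as separate terms, and the sentence that moves batch 2 on the attrition rate is removed.

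This needs no new procedure, and the planned 514 per condition is unchanged. The cost is the option to save participant payments by shrinking batch 2 early.

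Because the study is complete, the report should state which rate was used to size batch 2 and how many were retained per condition at each survey. If the early rate was used, the power should be restated for the number retained.

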## Study Design

Study Type: Interventional  
Primary Purpose: Supportive Care  
Study Phase: N/A  
Interventional Study Model: Factorial Assignment  
Number of Arms: 3  
Masking: None (Open Label)  
Allocation: Randomized  
Enrollment: 1328 [Actual]

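### The recruitment floor of 350 per condition does not match the sample-size calculation (357 to 360 analysed, 514 sampled), and the protocol does not say whether it is counted before or after attrition

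*Protocol*

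**What the plan says.** All the design figures are in the protocol's Study Description, under Detailed Description.

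- **Sample size.** The expected effect is a standardised difference of 0.19. The regression adjusts for the four baseline measures: "Under the assumption that these variables will account for at least 50% of the variance in the outcomes". The number needed "with 95% power is" 357, "or approximately 360 per condition".
- **Attrition.** The "expected attrition rate is 30% after baseline which means that the investigators will sample" 360/0.7 = 514 per condition.
- **Batches.** "The first batch will contain half the sample", namely 771, which is half of 3 x 514 = 1542. This batch is used to gauge attrition, with a pointer to the exclusion criteria. The second batch is then made smaller or larger according to what is seen.
- **Stopping.** If the number is still insufficient after that, "the investigators will repeat the process until at least 350 respondents in each experimental condition are recruited". The protocol adds that the number recruited per condition is the only consideration in stopping.
- **Timing.** Sampling is planned for a Sunday and, if needed, the Monday. Further weekly cohorts follow only if the number is still insufficient.

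The Study Design section records an actual enrolment of 1328.

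**The concern.** The sample-size paragraph sets two targets, one for respondents analysed (357, or about 360) and one for respondents sampled (514). The stopping rule introduces a third number, 350, which equals neither and is lower than both.

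The wording points to a count before attrition. The rule speaks of respondents recruited, and conditions are assigned at the end of the baseline survey, so a per-condition count exists from that moment. Recruitment is meant to close within about two days, when losses over weeks 1 to 5 cannot yet be seen. The six exclusion criteria under Eligibility concern the baseline survey or a respondent's declining to continue. Nothing in the floor itself adds back the 30% expected to be lost after baseline.

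The Eligibility section names adequate power as a central aim, and the study is intended as a registered report. The weight given to a null result there depends on the stated 95%. If recruitment could stop at a number that does not support that figure, a null result would be read as firmer than it is.

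**Working it through.** **Inputs from the protocol:** d = 0.19; variance explained R² = 0.50 (given as a minimum); power 95%; attrition 30%; floor 350.

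**Assumptions:** a two-sided 5% level, which the protocol does not state, and equal allocation, which the equal per-condition targets imply.

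**1. Reproduce the plan's figures.** With residual variance 1 − R² = 0.5 on the d scale,

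n per condition = 2 × (1.960 + 1.645)² × 0.5 / 0.19² = 360.

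The noncentral t version gives 361. Both agree with the stated 357 to 360. A one-sided 5% test would give 300, and R² = 0 would give 720, so neither explains the plan's figure. For attrition, 360/0.7 = 514.3, against the stated 514. The calculation is sound.

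**2. Power at the floor.** Power ≈ Φ( 0.19 / (√0.5 × √(2/n)) − 1.960 ).

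| Analysed per condition | How it arises | Power |
|---|---|---|
| 360 | the plan's rounded target; 514 × 0.7 | 95.0% |
| 357 | the plan's unrounded target | 94.8% |
| 350 | floor counted after attrition | 94.5% (noncentral t 94.4%) |
| 245 | floor counted before attrition, 350 × 0.7 | 84.5% (noncentral t 84.3%) |

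At 245 the type II error is about 16% instead of 5%. The effect detectable with 95% power rises from 0.19 to (1.960 + 1.645) × √0.5 × √(2/245) = 0.230.

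**3. Sensitivity to attrition, if 350 is counted before it.**

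| Loss | Analysed | Power |
|---|---|---|
| 10% | 315 | 92.1% |
| 20% | 280 | 88.9% |
| 30% | 245 | 84.5% |
| 40% | 210 | 78.6% |

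To retain even 350 at 30% loss, 350/0.7 = 500 per condition would have to be recruited.

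**4. The recorded enrolment.** 1328/3 = 442.7 per condition if equal. This yields 357 analysed only if attrition is at most 1 − 357/442.7 = 19.4%.

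**The case against.** The strongest answer is that 350 was meant net of attrition. The second batch is sized from the attrition seen in the first, in order to reach the desired number per condition. Such an adjustment makes most sense if the desired number is what remains, and the only such target in the protocol is about 360. A floor of 350 then looks like a small tolerance below it and costs about half a percentage point of power. This reading is tenable. The protocol does not state it, however, and even so the floor is under 357.

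The low-power case also needs an unlikely path. The floor is a fallback after two batches that default to 1542 in total. Stopping at 350 per condition before attrition means 3 × 350 = 1050 in total, hence only 1050 − 771 = 279 from the second batch if the first is kept whole. The protocol shrinks the second batch only when attrition is lower than expected, which sits badly with a 30% loss. Heavy baseline exclusions could bring the count down instead, but part of the gauged attrition might then already be accounted for. This stands, and it makes 84% a conditional worst case.

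Finally, 50% of variance explained is a minimum, so the powers above are lower bounds for given numbers analysed. Purely as an illustration, R² = 0.6 would give about 97.8% at 350 and about 91% at 245. This also stands.

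A reader might go further and infer from the 1328 enrolled, which is below 1542, that the trial fell short: at 30% loss about 310 per condition would remain, with power near 92%. The documents do not support that. They give neither the actual attrition nor whether 1328 was counted before or after exclusions, and a total below 1542 is what the batch rule prescribes if attrition ran below 30%.

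**Conclusion.** The inconsistency is real. The floor of 350 agrees with neither of the protocol's own targets, and the protocol leaves open which count it applies to. Its size depends on that count: about half a percentage point of power if respondents retained are meant, and about 10 to 11 points (95% to about 84%) if respondents recruited are meant, recruitment ends at the floor, and 30% are then lost. Both figures rest on a two-sided 5% test, equal allocation and R² exactly 0.50.

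It would be too strong to conclude that the trial was designed for, or ended with, 84% power. The default plan aims at 514 per condition, and the recorded enrolment, about 443 per condition if equal, did not end near 350 recruited. The supported conclusion is narrower: the sole stopping criterion is ambiguous, and on either reading its floor is below the number on which the 95% rests.

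**What to change.** State whether the floor counts respondents before or after attrition, and align it with the sample-size paragraph. Either of these would do:

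- stop when about 360 per condition are expected to be retained; or
- stop when 360/(1 − a) per condition have been recruited, where a is the attrition gauged from the first batch (514 at a = 30%).

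The two are equivalent and keep the adjustable second batch. They also fit the Sunday and Monday schedule, whereas a rule that waits for later outcome surveys would hold recruitment open for weeks. Because the pointer to the exclusion criteria leads to baseline events, the text should also say how loss after baseline enters a.

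If 350 is to stay, restate the power beside it: about 94% if retained, or about 84% if recruited with 30% loss, under the stated assumptions.

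As the study is recorded as completed, the practical step is to report which count was used to stop and to give precision (confidence intervals) from the numbers actually analysed in each condition, rather than lean on the planned 95%. The cost is wording only, with no enrolment beyond what the plan already foresees.

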## Conditions

Conditions: Happiness  
Anxiety  
Depression  
Morality

Keywords:

## Study Design

Study Type: Interventional  
Primary Purpose: Supportive Care  
Study Phase: N/A  
Interventional Study Model: Factorial Assignment  
Number of Arms: 3  
Masking: None (Open Label)  
Allocation: Randomized  
Enrollment: 1328 [Actual]

## Arms and Interventions

| Arms                              | Assigned Interventions |
|-----------------------------------|------------------------|
| No Intervention: Track activities |                        |

| Arms                                                                                                                                                                                                                                                                                                                                                                                              | Assigned Interventions                                                            |
|---------------------------------------------------------------------------------------------------------------------------------------------------------------------------------------------------------------------------------------------------------------------------------------------------------------------------------------------------------------------------------------------------|-----------------------------------------------------------------------------------|
| For three weeks research subjects will be keeping track of the things they do without altering their routine in any way.                                                                                                                                                                                                                                                                          |                                                                                   |
| Experimental: Self-focused acts
For three weeks research subjects will be “treating themselves” by doing things that they enjoy. These acts don’t have to be large or costly, but they should be over and above what they typically do. They are asked to do one (or more) things they enjoy each day for the first three days of each week and report them.                                   | Behavioral: Self-focused acts
Completion of daily acts for personal enjoyment. |
| Experimental: Prosocial acts
For three weeks research subjects are asked to perform acts of kindness, meaning behaviors that benefit someone else and are over and above what they typically do (i.e., they are not expected of them). These acts should also involve some sacrifice by them (e.g., in effort, energy, time, or money) and be completed for the first three days of each week. | Behavioral: Prosocial acts
Completion of daily acts for the benefit of others. |

